# Efficacy of silymarin in patients with non-alcoholic fatty liver disease — the Siliver trial: a study protocol for a randomized controlled clinical trial

**DOI:** 10.1186/s13063-023-07210-6

**Published:** 2023-03-10

**Keywords:** Clinical trial, Silymarin, Non-alcoholic fatty liver disease, randomized controlled trial

## Abstract

**Background:**

Non-alcoholic fatty liver disease (NAFLD) is one of the most prevalent liver diseases globally. Pharmacological treatments for NAFLD are still limited. Silymarin, a compound extracted from *Silybum marianum*, is an herbal supplement traditionally used in folk medicine for liver disorders. It has been proposed that silymarin may possess hepatoprotective and anti-inflammatory properties. The present trial aims to assess the efficacy of silymarin supplementation in the adjuvant treatment of NAFLD in adult patients.

**Method:**

This is a randomized double-blind placebo-controlled clinical trial recruiting adult NAFLD patients in therapy on an outpatient basis. Participants are randomized to an intervention (I) or control (C) group. Both groups receive identical capsules and are followed for 12 weeks. I receives 700mg of silymarin + 8mg vitamin E + 50mg phosphatidylcholine daily, while C receives 700mg maltodextrin + 8mg vitamin E + 50mg phosphatidylcholine daily. Patients undergo a computerized tomography (CT) scan and blood tests at the beginning and end of the study. Monthly face-to-face consultations and weekly telephone contact are carried out for all participants. The primary outcome assessed will be change in NAFLD stage, if any, assessed by the difference in attenuation coefficient between liver and spleen, obtained by upper abdomen CT.

**Discussion:**

The results of this study may provide a valuable opinion on whether silymarin can be used as adjuvant therapy for the management or treatment of NAFLD. The data presented on the efficacy and safety of silymarin may provide more foundation for further trials and for a possible use in clinical practice.

**Trial registration:**

This study has been approved by the Research Ethics Committee of the [name] University Hospital Complex, Salvador BA, Brazil, under protocol 2.635.954. The study is carried out according to guidelines and regulatory standards for research involving humans, as set out in Brazilian legislation. Trial registration - ClinicalTrials.gov : NCT03749070. November 21, 2018

## Strengths and limitations of this study

Placebo-controlled randomized double-blind clinical trial employing silymarin extract with greater bioavailability.The effectiveness of silymarin supplementation will be assessed by CT without contrast as reference standard for the detection and assessment of liver steatosis [1].Participants are recruited from a Nutrition and Hepatology Clinic of a single tertiary referral hospital.

## Introduction

### Background and rationale {6a}

NAFLD is one of the most prevalent liver diseases worldwide. With a continuously increased incidence and level of complications, NAFLD has become a major public health concern worldwide [2–4], with approximately 20% to 30% of the general adult population affected. Men appear to show a higher prevalence for NAFLD than women in all age groups [5]. Based on risk factors, NAFLD is manifested in approximately 50% of overweight individuals and in approximately 80% to 90% of obese individuals. Individuals diagnosed with metabolic syndrome (MS) are approximately twice as likely to develop NAFLD [6]. The main risk factors associated with NAFLD overlap with those of metabolic syndrome, including central obesity, type 2 diabetes (T2D), dyslipidemia, and insulin resistance (IR). NAFLD has been associated with a pro-inflammatory background and is considered a hepatic manifestation of obesity and MS [7, 8].

In its first stage, NAFLD patients show lipid inclusion in the liver parenchyma without evident signs of inflammation or hepatocellular necrosis. At this stage, NAFLD management is focused on improving IR, body fat reduction, as well as MS and T2D prevention and management. Body weight reduction combined with amelioration of metabolic disarrangements can prevent the progression of steatosis to non-alcoholic steatohepatitis (NASH), cirrhosis, and cellular hepatocarcinoma [9, 10].

Despite our understanding of the epidemiological and pathophysiological aspects of NAFLD, the main and by far most successful treatment option available is a positive lifestyle change. The use of pharmacological agents is still limited and requires stronger evidence regarding safety and efficacy [11]. As successful long-term adherence to positive lifestyle changes is not always achieved in full, researchers have investigated supporting pharmacotherapeutic strategies, such as herbal medicines, to ameliorate NAFLD. A few studies have suggested that silymarin supplementation may induce beneficial effects for NAFLD patients, including amelioration of biochemical markers associated with inflammation and NAFLD progression [12–15].

Silymarin is a flavonoid extracted from *Silybum marianum*, one of the most used medicinal herbs by individuals with liver diseases [16]. *Silybum marianum* has shown good tolerance and safety, with limited adverse effects reported in liver disease patients. The hepatoprotective, anti-inflammatory, antioxidant, and anti-fibrotic effects of silymarin have been studied in patients with cirrhosis associated with viral hepatitis, exposure to environmental toxins, alcoholic steatosis and NASH [17–20].

A few studies [13, 16, 18] have pointed out to a beneficial effect of silymarin therapy upon the evolution of NAFLD, but significant variability and methodological differences across available studies prevent the establishment of robust conclusions. A systematic review with meta-analysis [16] including six clinical trials showed that silymarin reduced serum levels of alanine aminotransferase (ALT) and aspartate aminotransferase (AST) in NAFLD patients, but the studies appraised in that meta-analysis had a high degree of heterogeneity and low methodological quality. The scarcity of clinical trials employing silymarin as adjuvant therapy for liver disease and NAFLD, with a particular attention to methodological design, planning, and execution stages, has encouraged us to propose and execute the Siliver trial. Our initial hypothesis is that silymarin supplementation will improve the metabolic status and reduce liver fat content in NAFLD patients. Our hypothesis will be tested by following the protocol detailed below.

### Objectives {7}

The present study aims to investigate the efficacy of silymarin supplementation as an adjunctive treatment for adult patients suffering with NAFLD. The primary outcome assessed will be change in NAFLD stage, if any, assessed by the difference in attenuation coefficient between liver and spleen, obtained by upper abdomen CT scan without contrast. The attenuation coefficient between the liver and spleen is a reference standard for the assessment of liver steatosis.

As secondary objectives, we will assess body mass index (BMI) and waist circumference (WC); glucose metabolism biomarkers including blood glucose, insulin, glycated hemoglobin (HbA1C), and Homeostasis Model Assessment-Insulin Resistance Index (HOMA-IR); blood ferritin levels; and biomarkers of liver damage, including transaminases, gamma-glutamyl transferase (γGT), and alkaline phosphatase (AP).

### Trial design {8}

As the trial hypothesis is to investigate whether silymarin supplementation is better than placebo for NAFLD amelioration, a framework of superiority was adopted for this double-blind randomized placebo-controlled clinical trial. Patients will be supplemented for 12 weeks (Fig. 1). The planning of this trial follows the guidelines of the Consolidated Standards of Reporting Trials (CONSORT) and Standard Protocol Items: Recommendations for Interventional Trials (SPIRIT) guidelines.

**Fig. 1 Fig1:**
[figure not shown]
Study flowchart

## Method: participants, interventions, and outcomes

### Study settings {9}

All participants had a confirmed NAFLD diagnosis prior to participation in this trial. NAFLD patients were referred to the trial by local health centers located in the neighborhoods of the city of Salvador BA Brazil, in partnership with our outpatient recruitment unit at the Nutrition and Hepatology Outpatient Clinic of the [name] University Hospital Complex (NHOC), located in the city of Salvador BA, Brazil, where the trial took place.

### Eligibility criteria {10}

#### Inclusion criteria

Eligibility criteria for the Siliver trial include consenting adult patients aged between 20 and 60 years of both sexes. All patients had a medically confirmed diagnosis of NAFLD prior to participation in this trial.

#### Non-inclusion criteria

Patients who meet any of the following criteria have not been included lactating or pregnant women, and women during their menacme, except for those who underwent definitive contraception such as hysterectomy or tubal ligation; patients with a previously established diagnosis of chronic disease including congestive heart failure, decompensated or severe lung disease, neoplasms, kidney disease, carriers of the human immunodeficiency virus (HIV), and advanced chronic liver diseases (Child-Pugh classification B and C) caused by any causal agent unrelated to NAFLD; recreational drug users; patients with an average intake of more than 20 g of alcohol per day and or a history of alcoholic disease in abstention for less than 6 months; use of prescribed medication including steroids, oestrogens, amiodarone, warfarin, anticonvulsants, antipsychotics, or chemotherapy drugs in the past 6 months; infections, surgery, trauma, or hospitalization in the past 30 days; chronic degenerative diseases of non-hepatic origin; and unavailability of previously obtained imaging tests with a diagnosis of NAFLD in its screening phase.

#### Exclusion criteria

The following patients will be excluded patients who at the recruitment stage do not show confirmation of NAFLD by CT scan; patients who missed any phase of the trial; and patients who during the trial were diagnosed with a condition listed in the non-inclusion criteria above.

### Who will provide informed consent? {26a}

Patients will provide informed consent themselves. All eligible participants have received information about the study and had the opportunity to have their questions answered to their satisfaction. The blinded evaluator has obtained written informed consent (IC) from all participants prior to assessment.

### Additional consent provisions for collection and use of participant data and biological specimens {26b}

The blood samples obtained, once analyzed for the specific purpose of this trial, are discarded following the Teaching Hospital Standard Operating Procedures (SOPs) on disposal of biological waste. Data collected from participants withdrawn from the study or lost on follow-up will be excluded and deleted, as the aim of the trial has not been completed for those participants. All participants have given their consent to the research team to share relevant data with researchers taking part in the research, as well as regulatory authorities. This set of information was explained to participants and made available in the consent form. All participants have agreed to the above.

## Interventions

### Explanation for the choice of comparators {6b}

Participants are randomized to groups intervention (I) or control (C). They receive identical capsules and follow the trial instructions for 12 weeks. All participants are instructed to take two capsules per day soon after a meal. Considering the pathophysiology of NAFLD and pharmacotherapies currently available for its treatment or management, there are no specific pharmacological agents currently approved for NAFLD specifically that could be compared to the test item. Therefore, the research team adopted a methodological design using a placebo.

### Intervention description {11a}

I participants receive 700 mg silymarin + 8 mg vitamin E + 50 mg phosphatidylcholine, daily. C participants receive 700 mg maltodextrin + 8 mg vitamin E + 50 mg phosphatidylcholine, daily.

Each I capsule contains 350 mg silymarin + 4 mg vitamin E + 25 mg phosphatidylcholine. Each C capsule contains 350 mg maltodextrin + 4 mg vitamin E + 25 mg phosphatidylcholine. All participants are instructed to take two capsules per day soon after a meal.

We have carefully defined the capsule composition for both groups to achieve a planned daily dosage. We employed phosphatidylcholine and vitamin E in the composition to increase silymarin bioavailability, which is based on a protocol described previously and evaluated in a systematic review with meta-analysis published by our group [15].

Microcrystalline cellulose, corn starch, and colloidal silicon dioxide were used as standard excipients in all capsules of both I and C. The capsule composition did not include dyes, preservatives or additives in I or C, guaranteeing the standardization of their appearance. The capsule weight, size, shape, and coating were identical between I and C, and have been designed to ensure the same ease of swallowing, to minimize risks of gastric discomfort for the participants, and to ensure similar disintegration time and propensity for swelling. The capsules are visually unidentifiable between I and C. All I and C capsules were manufactured and kindly donated by Singular Pharma (Salvador, Brazil). The expiry date is three months after production.

### Criteria for discontinuing or modifying allocated interventions {11b}

Participants are free to withdraw from the trial at any time and for any reason without penalty. Participants are withdrawn from the study if they start a different treatment elsewhere.

### Strategies to improve adherence to interventions {11c}

Participants are monitored weekly by telephone calls to collect information on adherence. They are given the opportunity to ask the research team any question and receive reminders of upcoming appointments. In addition, participants are instructed to bring along the latest flasks with the capsules received at each appointment, favoring greater adherence and commitment to the treatment.

### Relevant concomitant care permitted or prohibited during the trial {11d}

During the intervention and follow-up, participants are advised not to use any medication, supplement, tea or herbal supplement without prior medical and nutritional advice, and without prior notice to the research team. If they do, they are asked to inform the research team immediately, informing what was ingested and the date and dosage taken.

### Provisions for post-trial care {30}

All study participants have the right to medical care and follow-up, and if they experience a worsening of their condition. In the final consultation, participants who no longer show fatty infiltration receive guidance on how to prevent the recurrence of NAFLD. Participants who show evidence of NAFLD, regardless of the degree of steatosis, are referred to the outpatient follow-up clinic for the continuation of their care provision with a hepatologist consultant and a nutritionist (Fig. 1).

### Outcomes {12}

#### Primary outcome

The primary outcome will be the assessment of NAFLD resolution, or change in its grade, as assessed by the difference in the attenuation coefficient between liver and spleen, obtained by CT of the upper abdomen, at the end (after) compared to beginning (before) the trial. In summary, the primary outcome is to investigate whether silymarin supplementation can reduce liver fat content in NAFLD patients, measured by a CT scan.

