### Sample Size {14}

The sample size was determined through an accuracy analysis of the primary outcome. A significance level of 0.05 and a power of 80% were adopted, which resulted in a minimum sample size of approximately 132 participants.

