## Intervention assignment: allocation

### Sequence generation {16a}

Patients who agreed to take part in the study and met all the study criteria were assigned to I or C groups by computer-generated randomization in blocks with the aid of a spreadsheet to ensure a random but uniform variation in sizes of each I and C blocks. Randomization and record keeping of all participants were carried out by a statistician researcher external to the research group. The statistician is not involved in patient clinical assessment.

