## Statistical methods

### Statistical methods for primary and secondary outcomes {20a}

Statistical analyses will firstly be performed using descriptive analysis to characterize the distribution of the events studied. Categorical variables will be investigated using simple absolute frequencies. Continuous variables will be investigated by measures of central tendency and dispersion. Parametric or non-parametric tests will be used considering the distribution nature of the variables studied. A significance level of 5% will be adopted for all statistical tests. Tests to verify variable behavior and comparisons of proportions analyses, such as the application of the chi-square test or Fisher’s exact test, will be discussed later with a qualified statistician. Tests for comparison of means between groups, analysis of correlations between continuous variables and logistic regression analysis, will also be discussed with the statistician. Data will be tabulated and analyzed using the R Project for Statistical Computing software (R-3.2.4 for Windows).

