### Interim analyses {21b}

This is a low-risk intervention, as silymarin at the dosage adopted in this trial has been considered safe and well-tolerated. All patients were carefully followed up in person and by telephone, aiming to identify any adverse event. Only patients who successfully complete the trial will have their data included in the final data analyses.

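### The single primary outcome is worded both as a categorical change (stage, grade or resolution) and as a reduction in liver fat, and nothing in the protocol says which version decides the trial

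*Protocol article*

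**What the plan says.** The protocol article describes its one primary outcome in three places.

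- Objectives {7}, with the same wording in the Abstract: "The primary outcome assessed will be change in NAFLD stage, if any", judged by the liver–spleen attenuation difference on CT. Resolution is not mentioned.
- Outcomes {12}, first sentence: "The primary outcome will be the assessment of NAFLD resolution, or change in its grade, as assessed by the difference in the attenuation coefficient", end of trial against beginning.
- Outcomes {12}, closing summary: "the primary outcome is to investigate whether silymarin supplementation can reduce liver fat content in NAFLD patients, measured by a CT scan". The hypothesis at the end of the Background is also framed as a reduction in liver fat.

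Four other sections bear on the choice.

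- The secondary outcomes contain no CT variable.
- Section {20b} rules out additional analyses.
- Section {20a} mentions tests of proportions, comparisons of means and logistic regression, leaves the choice for later discussion with a statistician, and adds: "A significance level of 5% will be adopted for all statistical tests".
- Sample Size {14} says: "The sample size was determined through an accuracy analysis of the primary outcome" and "A significance level of 0.05 and a power of 80% were adopted, which resulted in a minimum sample size of approximately 132 participants". It does not say which version of the outcome was used.

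**The concern.** All the wordings rest on one measurement, but they do not define one variable. A change of stage or grade is categorical, resolution is a yes/no event, and a reduction in fat content reads as a quantity. Each needs its own summary measure and test, and they can disagree. Attenuation can improve without crossing a grade boundary, and a grade can fall without resolution.

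No CT variable is listed as secondary and no further analyses are planned, so every CT version sits under the primary label. Two things are at stake. The 5% error rate of the main claim is not protected while the choice is open, and the stated 80% power has no definite meaning until the variable is named.

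**Working it through.** **1. The stated figure.** The total of 132 cannot be reproduced from the document, which gives no difference, SD or rate. Back-solving, assuming two-sided 5%, 80% power and 1:1 allocation (66 per arm, inferred from "computer-generated randomization in blocks with the aid of a spreadsheet to ensure a random but uniform variation in sizes of each I and C blocks"):

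- Two means: n per arm = 2(1.960 + 0.842)²/d². With d = 0.49 SD this is 15.70/0.2401 = 65.4, rounded up to 66, so 132 in total. The smallest detectable shift at 66 per arm is 2.802 × √(2/66) = 0.488 SD.
- Two proportions, 30% against 54% (mean 42%): n per arm = [1.960√(2 × 0.42 × 0.58) + 0.842√(0.3 × 0.7 + 0.54 × 0.46)]²/0.24² = 65.2, rounded up to 66, so again 132.
- Precision of one proportion of 50% with half-width 8.5 points: 1.960² × 0.25/0.085² = 132.9, rounded up to 133.

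The sample size therefore fits a continuous and a categorical endpoint equally well and does not show which was meant.

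**2. Type I error if success on any version counts.** For independent tests the reference values are 1 − 0.95² = 9.75% for two versions and 1 − 0.95³ = 14.3% for three. The versions share one measurement, so the real figure is lower. It was simulated under these assumptions:

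- 66 per arm, with every participant contributing a result (the plan analyses completers only).
- Baseline severity normal with mean 0.8 and SD 1, truncated at the diagnostic threshold 0.
- Change normal with mean −0.3 and SD √(2(1 − ρ)) in both arms, where ρ stands for the baseline–final correlation.
- Grade boundaries at 0, 1 and 2; resolution means a final value below 0.
- Three two-sided 5% tests: mean change, resolution yes/no, grade improved yes/no.
- 8,000 null trials per ρ.

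| ρ | any of three, either direction | any of three, favouring silymarin (nominal 2.5%) |
|---|---|---|
| 0.5 | 10.7% | 5.2% |
| 0.7 | 11.3% | 5.3% |
| 0.85 | 11.8% | 5.5% |

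Each test alone stayed near 5%. A second simulation, with grade boundaries 0.75 SD apart and ρ from 0.6 to 0.8, gave 10.5–12.2% in either direction.

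**3. Power of each version.** Same set-up, with a treatment shift of 0.488 SD of the change and 4,000 trials per ρ:

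| ρ | continuous change | ordinal grade change | grade improved yes/no | resolution |
|---|---|---|---|---|
| 0.5 | 79% | 65% | 55% | 43% |
| 0.7 | 80% | 63% | 52% | 34% |
| 0.85 | 79% | 56% | 47% | 27% |

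A cross-check without simulation applies the same shift to a yes/no endpoint with control rate p, so that the treated rate is Φ(0.488 + z_p). With 66 per arm:

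| control rate | treated rate | power | total N for 80% |
|---|---|---|---|
| 5% | 12.4% | 32% | 458 |
| 10% | 21.4% | 43% | 320 |
| 20% | 36.2% | 54% | 242 |
| 30% | 48.5% | 59% | 216 |
| 50% | 68.7% | 59% | 214 |

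**4. Information kept.** This is approximately (1.960 + z_power)²/(1.960 + 0.842)². At 54% power it is 2.060²/7.85 = 54%. At 56–65% power it is about 57–70%.

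**The case against.** The strongest defence is that there is only one measurement and one ordered scale. Resolution can be read as the lowest grade, and the sections on post-trial care and the final consultation do separate patients with no remaining fatty infiltration from those with any degree of steatosis. The summary sentence can be read as an aim rather than a variable. This has force: a reader who counts three distinct endpoints is taking the least charitable reading. What survives is a categorical version and a continuous one, with no rule between them.

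Other tempting inferences go beyond the text.

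- A reader might conclude that the trial's type I error is about 11%. No section says that success on any version makes the trial positive, and the 5% sentence sets a general level, not a multiplicity rule. The inflation is conditional.
- A reader might say that the categorical versions throw away most of the information. For grade, about half or more is kept in most of the scenarios tried; only resolution alone loses most, and the protocol does not make it the sole endpoint.
- A reader might say that 80% power can hold for only one version. No effect is stated, and a larger one could bring several versions above 80%.
- A reader might fault the absence of attenuation cut-offs for the grades. An article can leave these to the full protocol, to which section {31c} refers, so this is no finding.

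An ordinal grade endpoint would also be a defensible choice, and it is closer to the Abstract and Objectives.

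**Conclusion.** The concern holds in a limited form. The protocol's own statement of its primary outcome is inconsistent between the Abstract and Objectives on one side and Outcomes on the other, and within Outcomes itself. An analysis plan could pick one version, but it would still conflict with part of this text.

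If the choice followed the data, or any success counted, type I error would be roughly doubled: about 11% in either direction, about 5% in silymarin's favour against 2.5%. These figures count three versions. With resolution folded into grade only two remain, and the inflation stays below the 9.75% reference for two independent tests.

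The power figures assume a shift of about 0.49 SD, normal changes, 1:1 allocation, and assumed correlations and grade spacing. Their size is illustrative. Their direction, with less power for the categorical versions than for the continuous one, held in every scenario tried. The stated 80% therefore depends on which version is meant.

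**What to change.** Name one primary variable. The preferred choice is the between-group difference in liver-minus-spleen attenuation (HU) at the end-of-treatment CT, adjusted for baseline. Make grade change and resolution secondary. Use the same wording in the Abstract, Objectives {7} and Outcomes {12}, and state in Sample Size {14} which variable the 132 refers to.

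Date the change and say whether it was made before unblinding. Recruitment ended in May 2022, and allocation envelopes are to be opened once the last participant completes, so the article does not show whether that window is still open. If unblinding has already occurred, say so and report all versions.

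The cost is a wording change plus a registry and ethics update. No new data are needed, because both CT scans are already part of the schedule. The downside is small: the clinically familiar grade change becomes a secondary result.
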